### Control group

Participants assigned to the control group will receive usual care, i.e., no exercise intervention. They will be asked to maintain their habitual physical activity pattern.

After completion of the present study, the control subjects will be offered participation in a rehabilitation programme for cancer survivors [21-23].

### Study endpoints

At baseline, at 18 weeks and at 9 months study participants will visit the study centre for outcome assessment (see Figure 2). During the entire 9 months, once a week, participants will fill out diaries to assess their healthcare use and work status. Participants will be asked to wear a pedometer during seven days once following baseline measurements and again after 18 weeks and after 9 months. Participants of the exercise group fill out exercise logs. The following data will be collected:

demographics (gender, age, hospital, name of medical specialist) and factors related to cancer (type of cancer; treatment regime). More detailed information regarding diagnosis and the treatment regime will be collected from medical records.

#### Primary outcomes

Fatigue will be measured using the Multidimensional Fatigue Inventory (MFI) and the Fatigue Quality List (FQL) [24,25]. The MFI is a 20-item self-report instrument designed to measure multiple fatigue characteristics and the impact on function. The Dutch version of the MFI has proven to be valid and consists of five subscales (general fatigue, physical fatigue, reduced activity, reduced motivation and mental fatigue) [24].

The FQL consists of 28 adjectives addressing the perception of fatigue [25]. Participants are asked to mark which out of 28 adjectives fit their experienced fatigue. Multiple answers are possible. The adjectives are clustered in four subscales: frustrating, exhausting, pleasant and frightening.

To register health service utilisation and sick leave participants will keep diaries. Diaries will include all types of health care consumption also including contacts with alternative medicine and own out of pocket expenses. Participants will be asked to keep track of their absence from work (if applicable).

The diaries include also a multidimensional measurement of health status, the EuroQuol-5D (EQ-5D). The EQ-5D will be used to calculate quality adjusted life years (QALYs) and consists of the EQ-5D descriptive system and the EQ VAS [26]. The EQ-5D descriptive system comprises five dimensions of health (mobility, self-care, usual activities, pain/discomfort anxiety/depression). Each dimension comprises three levels (no problems, some/moderate problems, extreme problems). The EQ VAS records the respondents self-rated health status on a vertical graduated (0-100) visual analogue scale.

#### Secondary outcomes

To measure health related quality of life the European Organisation Research and Treatment of Cancer-Quality of Life-C30 questionnaire (EORTC-QoL-C30) (version 3) and the Short Form 36 healthy survey (SF-36) will be used. Both questionnaires have been validated [27-29].

The EORTC QOL C30 incorporates five functional scales (physical, role, emotional, cognitive and social functioning), one quality of life scale and one symptom scale (including fatigue and pain). The SF-36 consists of 36 items, organised into eight scales: physical functioning, role limitations due to physical health problems, bodily pain, general health perceptions, vitality, social functioning, role limitations due to emotional problems and general mental health.

The perceived impact of the disease on participation and autonomy will be measured with the validated Impact on Participation and Autonomy (IPA) questionnaire [30,31]. The IPA incorporates 32 items clustered in the subscales autonomy indoors, family role, autonomy outdoors, social life and relationships, and work and education.

Anxiety and depression will be self-rated with the Dutch language version of the Hospital Anxiety and Depression Scale (HADS) [32]. The HADS consists of 14 items, seven items of the depression subscale (HADS-D) and seven items of the anxiety subscale (HADS-A).

Physical fitness will be assessed as aerobic peak capacity and muscle strength. Aerobic capacity will be determined using a symptom-limited bicycle ergometry test with breathing gas analysis using a ramp 10-, 15-, or 20-protocol, dependent on the patient's condition. The load will be increased every minute in such a way that patients reach peak workload within 10 minutes. The test will be terminated on the patients' symptoms or at the physicians' discretion. Borg scores for dyspnoea and muscle fatigue will be taken before and after the test. Peak workload, peak oxygen uptake and Borg scores at peak workload will be taken for analysis. Heart rate and work load at ventilatory threshold will be used to determine the work load for the aerobic training during the exercise programme.

Muscle strength of quadriceps and hamstring will be assessed by using a Cybex dynamometer at 60°/s and 180°/s. After a standardised 5-minute warm-up, five repetitions will be performed to practice before the definitive measurements at 60°/s and 180°/s will be taken. Between all sessions, there will be a 1-minute rest period. The patient will be verbally encouraged. The highest peak torque value of three repetitions for both velocities will be calculated. The fatigue index comparing the first and the last of fifteen repetitions will be calculated at 180°/s.

Handgrip strength of both hands will be measured with a mechanical handgrip dynamometer. The best score of two attempts will be recorded in kilogram force (kgF).

The Body Mass Index (BMI) will be calculated as weight in kilograms divided by height in meters squared (kg/m^2^). Body weight and height (to the nearest 0.5 kg and 0.5 cm respectively) will be measured while the subjects wear light clothes and no shoes using an analogue balance (SECA) and wall mounted tape measure, respectively.

Body fat distribution will be estimated by the waist- and hip circumference. Waist circumference (to the nearest 0.5 cm) will be measured standing at the smallest circumference between abdomen and chest. Hip circumference (to the nearest 0.5 cm) will be measured standing as the largest circumference between waist and thigh. All measurements will be taken in duplicate and averaged.

Self efficacy about the performance of physical activity will be assessed by seven (exercise programme) or eight (exercise recommendation) items based upon the Social Cognitive Theory. Items will be scored on a 5-point Likert scale with endpoints labelled 'strongly disagree' and 'strongly agree'.

Physical activity level will be measured using the Short Questionnaire to assess health enhancing physical activity (SQUASH) [33].

To monitor the physical activity level, participants of the intervention group will also be asked to keep an exercise log during the 18-week exercise programme. In the log, they register the frequency, intensity, and duration of the exercises they were performing during the study period. In addition, physical activity will be measured by a pedometer. Participants, of both the intervention and the control group, will wear the pedometer during seven days following their baseline and follow-up measurements.

The attendance rate for the exercise sessions will be recorded in a Case Record Form.

Adherence to the exercise recommendation will be registered in the exercise log.

Adverse events reported spontaneously by the subject or observed by physiotherapists, study nurse or medical doctor will be recorded, i.e. sports accidents, surmenage, or injuries. All serious adverse events will be reported to the accredited ethical committee that approved the protocol, according to the requirements of that ethical committee.

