## Methods/Design

### Design

The PACT-study examines the effects of exercise during cancer treatment on reducing complaints of fatigue and in reducing health service utilisation and sick leave (primary outcomes). In addition, we will study the effects on improving health related quality of life, impact on autonomy and participation, anxiety and depression, physical fitness, body composition and cognitive-behavioral aspects (secondary outcomes). This study is designed as a multicentre pragmatic randomised controlled trial, with two study arms, i.e. a group invited for an exercise programme in addition to usual care; and the control group receiving usual care while maintaining their habitual physical activity pattern. The exercise programme is an 18-week supervised group programme. Because blinding of participants towards allocation is not feasible, this study has a pragmatic design.

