### Exercise Intervention

The exercise programme is designed by applying the principles of 'Intervention Mapping' [15]. Intervention Mapping provides a framework for effective decision making in the developmental process of (health promotion) interventions using five steps: 1) specification of objectives, 2) development of methods and strategies, 3) design of the programme, 4) anticipation of implementation and 5) evaluation. The exercise objectives, specified for the specific target population were set by an in-depth literature search and by seeking advices of medical oncologists, radiotherapists and a surgeon. Subsequently, the exercise methods were developed in close cooperation with physiotherapists experienced in rehabilitation programmes for cancer survivors. This resulted in a clear exercise programme and materials for instruction for physiotherapists as well as information leaflets for patients. We continuously involved medical specialists and physiotherapists in the development in order to optimise implementation of the exercise programme in the health care system.

The exercise programme will be offered at several outpatient clinics of general hospitals. Participants will attend this programme twice a week. The programme incorporates principles for aerobic training and muscle strength training as well as principles of Bandura's social cognitive theory [16].

The programme will be individualised to the patient's personal preferences and physical fitness level. During an intake prior to the exercise programme, information about patient's preferences, regular sports activities, requirements at home and work, and physical fitness level (by means of a symptom limited exercise test and 1-repetition maximum (1-RM) muscle strength tests) and physical limitations will be collected by the physiotherapist. After the intake, the patient will start the 18-week exercise programme. The 1-hour exercise classes will include a warming up (5 min), aerobic and muscle strength training (50 min) and a cooling down (5 min). *Aerobic training *includes interval training of alternating intensity at or below the ventilatory threshold (3 × 2 min increasing to 2 × 7 min) as determined during the baseline symptom limited bicycle ergometry test (see study end points, secondary outcomes). Heart rate and the Borg scale of perceived exertion will be monitored during the aerobic training.

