*Muscle strength training *will be performed for all major muscle groups: arms, legs, shoulders, and trunk: 2 × 10 repetitions (65% 1-RM) increasing to 1 × 10 repetitions (75% 1-RM) and 1 × 20 repetitions (45% 1-RM).

The exercise programme incorporates principles of Bandura's social cognitive theory (SCT) to help participants maintaining a physically active lifestyle during and after cancer treatment [16]. This theory emphasises the role of cognitive processes in determining behaviour such as exercise. The most important construct in the theory is self-efficacy that is defined as "an individual's beliefs in his/her capabilities to organise and execute the course of action required to produce given attainments" [16]. The concept has been used successfully in other intervention studies that aim to alter health related behaviour [17]. Self efficacy will be altered using three different techniques, namely actual or mastery experience, vicarious or observational experience and verbal persuasion. First, actual or mastery experience will be used by asking participants to report training results in graphs. Physiotherapists will check these weekly and give positive feedback about the obtained results and will stimulate the participant to make action plans to further increase their exercise level. The starting point of the training schedule has been carefully chosen so it will be likely that the participant will succeed and subsequently have a mastery experience in doing physical exercises.

Vicarious or observational experience is applied by using DVDs where other cancer patients show their experiences with exercise programmes. Also the use of a so-called buddy will help in role modelling as a component of the programme. The buddy is a senior participant introducing a new participant to the programme. During the programme they will work together and support each other when facing difficulties in executing the exercises. Finally, verbal persuasion is used. Physiotherapists will strongly recommend exercise which will be supported by written information.

In addition to the supervised exercise programme twice a week, patients are recommended to be physically active for at least 30 minutes a day, five days a week according to the Dutch guideline for physical activity [18], which is based on international recommendations [19,20]. This should include an aerobic component of moderate intensity in agreement with the participant's fitness and desires.

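### One named adverse-event source, programme physiotherapist observation, exists only in the exercise arm, so any between-arm comparison of non-serious event counts would be open to detection bias

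*Protocol article*

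**What the plan says.** The rule for adverse events is at the end of the Secondary outcomes section: "Adverse events reported spontaneously by the subject or observed by physiotherapists, study nurse or medical doctor will be recorded". The kinds of event follow: "i.e. sports accidents, surmenage, or injuries". Serious events have their own sentence, which makes no distinction by arm: "All serious adverse events will be reported to the accredited ethical committee that approved the protocol".

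The contact schedule is given elsewhere in the article:

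- **Exercise arm.** Design: "The exercise programme is an 18-week supervised group programme". Exercise Intervention: "Participants will attend this programme twice a week". The same section adds a weekly review of participants' training graphs: "Physiotherapists will check these weekly and give positive feedback about the obtained results".
- **Control arm.** Control group: "Participants assigned to the control group will receive usual care, i.e., no exercise intervention".
- **Both arms.** Study endpoints sets visits at baseline, 18 weeks and 9 months, and a diary: "During the entire 9 months, once a week, participants will fill out diaries to assess their healthcare use and work status". Primary outcomes adds the EQ-5D to the diary. Neither section names the diary as a source of adverse events.

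**The concern.** A fair comparison of event counts needs events to be looked for in the same way in both arms. Here one of the named observers is part of the intervention. An overstrained muscle or a stumble in a supervised class happens in front of someone who is to record it. The same event in a control participant at home is recorded only if the participant mentions it or if the study nurse or a doctor notices it. The listed event types are also those that a physiotherapist in a class is best placed to see.

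At stake is how the safety of the programme will be read. The Discussion names standardised exercise programmes as the next step if the trial succeeds, and readers will look at event counts by arm whether or not a test is attached. An excess in the exercise arm could not then be divided into what exercise caused and what closer observation revealed. Later analysis cannot repair this, because control-arm events that were never recorded cannot be recovered from the data.

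**Working it through.** The article gives no adverse-event rate, safety margin or safety power, so there is no figure to reproduce. The check sets the sources side by side, counts the contacts that differ, and then asks what can be said about direction and size.

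**1. Sources by arm**

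| Source named in the adverse-event sentence | Exercise arm | Control arm |
|---|---|---|
| Spontaneous report by the participant | yes | yes |
| Study nurse | yes | yes |
| Medical doctor | yes | yes |
| Programme physiotherapist | yes | no |

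Three of the four sources are shared. The inequality lies in the fourth.

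**2. Extent of the unshared source**

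- Full attendance: 2 sessions per week × 18 weeks = 36 sessions.
- At the 75% attendance that defines the per-protocol group (Data analysis): 0.75 × 36 = 27 sessions.
- At the lowest attendance among pilot completers, 50% (Preliminary results): 0.50 × 36 = 18 sessions.

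This source runs for 18 of roughly 39 weeks of follow-up (9 × 52/12 = 39). After the programme ends, the named sources are the same in both arms.

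**3. Direction**

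Let c be the share of events found through the three shared sources, taken as equal in both arms. Let p be the share of the remaining events that physiotherapists find in the exercise arm.

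- Control detection = c
- Exercise detection = c + p(1 − c)
- Ratio of recorded to recorded, at equal true risk = 1 + p(1 − c)/c

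The ratio exceeds 1 whenever p > 0 and c < 1. The bias therefore points towards apparent harm from exercise. More frequent contact also gives exercise participants more occasions to mention an event, which acts in the same direction.

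**4. Size**

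The article supplies neither c nor p. With purely assumed values the ratio is:

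- c = 0.9, p = 0.25: 1 + 0.25 × 0.1/0.9 = 1.03
- c = 0.5, p = 0.5: 1 + 0.5 × 0.5/0.5 = 1.50
- c = 0.3, p = 0.75: 1 + 0.75 × 0.7/0.3 = 2.75

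The spread runs from negligible to large. It shows that the document does not fix the size, and no value in it is an estimate for this trial.

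**5. Is there a planned comparison?**

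Adverse events are absent from the secondary outcomes listed in the Abstract and under Design, although the sentence about them stands below the Secondary outcomes heading. Data analysis describes testing of fatigue and no between-arm analysis of adverse events.

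**The case against.** The strongest reply is that the article promises only to record these events. With no comparison planned, there is none to be biased. The listed types are the hazards of the exercise programme itself, and watching for them during sessions is a sensible way to monitor an intervention. This stands, and it limits the point to what happens if counts are compared.

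A second reply is that controls are far from unobserved. Study nurse and doctor are named in the same sentence, spontaneous reporting is not tied to visits, and all participants are scheduled for chemotherapy and so have clinical contact. The diaries of both arms would show an injury that led to care or to absence from work, and the fatigue questionnaires cover exhaustion in both. This also stands in part. A reader might infer that controls have no observer, or can report only at the two follow-up visits; the article supports neither. The diary and questionnaires are nevertheless not named as adverse-event sources, and a minor event that led to no care or absence need not appear in the diary.

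A third reply is that an article condenses the full protocol, which may hold an equal enquiry. That is possible, and the absence of such an enquiry alone would be no finding. But the article does more than stay silent: it names the sources, and one of them is confined to one arm.

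**Conclusion.** The point holds in a limited form. The stated method of finding adverse events is unequal between arms because programme physiotherapists, at up to 36 sessions, observe the exercise arm only, and no enquiry put equally to both arms is described. Any between-arm comparison of non-serious event counts would be open to detection bias towards apparent harm from exercise.

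Two stronger readings are tempting and should not be drawn. One is that the trial's safety comparison is biased; the article plans no such comparison. The other is that a particular false risk ratio can be expected; every such figure rests on assumed detection rates, and the size cannot be determined from the document.

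The direction rests on two assumptions: that the shared sources work about equally well in both arms, and that physiotherapists record at least some events that those sources would miss. Serious events are outside the point, since their reporting is not tied to the sessions. This is an inexpensive improvement to data collection and does not affect the primary outcomes.

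**What to change.** - Add one fixed adverse-event question with a short checklist (injury, fall, exhaustion, other) to the weekly diary, identical in both arms, for the full nine months.
- State that any between-arm comparison of adverse events will rest on these solicited answers.
- State that events observed at exercise sessions will be reported descriptively, for the exercise arm only and without comparison with controls.
- Leave serious-event reporting as written.

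If the full protocol already contains an equal enquiry, only the second and third statements are needed.

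The cost is one or two diary lines and one extra table, with no additional staff, visits or procedures. The downside is a slightly longer weekly diary and more minor events on record. The question has to be in the diary when it is issued, because the analysis stage cannot supply it.

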### Sample size

In accordance with previous studies [34], we consider an effect of a 2-unit improvement in the MFI questionnaire to be clinically relevant. To detect an intervention effect of 2 units of change (± SD 4) in fatigue (MFI questionnaire (range subscale 4-20)) we will need 75 participants in the intervention and control group for each cancer type, 300 participants in total (alpha = 0.05, power = 0.80). A drop-out of 10% is anticipated. The proposed number of participants also allows us to perform analyses for the two types of cancer separately.

This sample is also large enough to detect a clinically relevant intervention effect of 10 units of change (± SD 20) on the secondary outcome EORTC QLQ C30 subscales [35].

### Data analysis

Descriptive statistics will be used to characterise the study population and the instrument scores at baseline and at the follow up measurements. Mean differences including 95% confidence intervals will be calculated. Mean differences will be presented for the total study population and for different subgroups (cancer type, cancer regime). The effect of physical exercise on fatigue will be tested at 18 weeks (end of the exercise programme) and nine months post-enrolment according to the intention to treat principle (primary analyses), and on a per protocol basis including participants of the exercise group who attended at least 75% of the exercise sessions. Longitudinal analyses will be conducted, using mixed linear regression models while taking different levels (time and hospital) into account [35]. In the longitudinal analyses the programme accounts for missing data based on the observed data.

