### Recruitment and Allocation

Patients will be recruited by medical specialists and specialised nurses in at least six hospitals in the regions of the Comprehensive Cancer Centers Middle Netherlands, Limburg and Rotterdam. New cancer patients will be informed and invited by the clinician or the oncological nurse during a regular outpatient clinic visit. Patients willing to participate will be asked to visit the study centre to assess study eligibility and for baseline measurements. If eligible, patients will be asked to sign informed consent upon which they will be randomly allocated to the intervention or the control group by central data management. Allocation to the intervention- or control group will be concealed. Randomisation will be stratified per tumour site (breast or colon) by the sequential balancing method. The following characteristics will be balanced: age (25-40, 40-65 and 65-75 years), adjuvant treatment (radiotherapy versus no radiotherapy (before chemotherapy)); using a tissue expander (for breast cancer patients yes versus no) and hospital. For colon cancer patients, gender will be included as a first step in above balancing algorithm. Recruitment and allocation strategy is summarised in Figure 2.

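### The fatigue mixed model, as described, names only time and hospital. Adding baseline fatigue, tumour site (pooled result) and the other balancing factors would gain precision at almost no cost.

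*Protocol article*

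**What the plan says.** **Allocation.** Under Recruitment and Allocation, the protocol article states: "Randomisation will be stratified per tumour site (breast or colon) by the sequential balancing method". The factors balanced are age in three bands, radiotherapy before chemotherapy, "using a tissue expander (for breast cancer patients yes versus no) and hospital". It adds: "For colon cancer patients, gender will be included as a first step in above balancing algorithm".

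**Measurement.** Under Study endpoints: "At baseline, at 18 weeks and at 9 months study participants will visit the study centre for outcome assessment". Fatigue is a primary outcome, so a baseline score is planned for every participant.

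**Analysis.** Under Data analysis: "Mean differences including 95% confidence intervals will be calculated", for the total population and for subgroups that include cancer type. Then: "The effect of physical exercise on fatigue will be tested at 18 weeks (end of the exercise programme) and nine months post-enrolment", by intention to treat as the primary analysis. The longitudinal analyses are done "using mixed linear regression models while taking different levels (time and hospital) into account". The section lists no covariates, and mentions baseline scores only under descriptive statistics.

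**Sample size.** The Sample size section plans for 2 units of change with SD 4 on an MFI subscale, alpha 0.05, power 0.80 and 10% drop-out, with 75 per arm for each cancer type. It says that this number also allows the cancer types to be analysed separately.

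**The concern.** Two sources of precision are available, and the model description uses neither in full.

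- **Balancing factors.** Balancing on prognostic factors removes most of the chance difference between arms on those factors. A model that omits them still counts their variance in the standard error. The interval is then too wide and the test rejects too rarely under the null. Hospital is carried into the model. Age group, radiotherapy, tissue expander and gender are not named, and tumour site appears only as a subgroup.
- **Baseline score.** Baseline fatigue is likely to predict later fatigue. The Data analysis section does not say whether the mean differences are of follow-up scores, changes or baseline-adjusted means. The sample size section speaks of change, but the model description does not carry this through.

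At stake is efficiency in the primary fatigue comparison. The false-positive rate is not at risk.

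**Working it through.** **Inputs from the Sample size section:** difference 2, SD 4, alpha 0.05 (two-sided assumed), power 0.80, drop-out 10%, 75 per arm per cancer type. **Assumed, because the documents give no figure:** correlation r between baseline and follow-up fatigue, 0.3 to 0.7; share of outcome variance R² explained by the omitted balancing factors, 0.05 to 0.20.

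**1. The plan's own figure.** n per arm = 2(1.960 + 0.842)² × 4²/2² = 62.8, so 63; 63/0.9 = 70. The exact t-test needs 64; 64/0.9 = 71.1, so 72. The stated 75 is slightly more than its inputs require. After 10% loss, 75 × 0.9 = 67.5, taken as 67.

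**2. Power without adjustment.** SE = 4√(2/67) = 0.691; 2/0.691 = 2.894; power = Φ(2.894 − 1.960) = 0.825 (0.819 by t-test). The planned 80% is met if SD 4 is the SD of whatever is compared.

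**3. Baseline adjustment.** The residual SD after adjustment is σ√(1 − r²), where σ is the SD of the follow-up score.

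- If SD 4 is the follow-up SD, σ = 4. A raw change then has SD 4√(2(1 − r)).
- If SD 4 is the SD of change, σ = 4/√(2(1 − r)), and the adjusted SD is 4√((1 + r)/2).

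Power at 67 per arm:

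| Reading of SD 4 | Quantity compared | r = 0.3 | r = 0.5 | r = 0.7 |
|---|---|---|---|---|
| Follow-up SD | Follow-up score | 0.825 | 0.825 | 0.825 |
| Follow-up SD | Raw change | 0.686 | 0.825 | 0.962 |
| Follow-up SD | Baseline-adjusted | 0.859 | 0.916 | 0.982 |
| SD of change | Follow-up score | 0.928 | 0.825 | 0.611 |
| SD of change | Raw change | 0.825 | 0.825 | 0.825 |
| SD of change | Baseline-adjusted | 0.948 | 0.916 | 0.881 |

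The baseline-adjusted row is the best within each reading at every r shown, and it stays above 0.80 throughout. An unadjusted comparison falls below 0.80 only where SD 4 does not belong to the quantity compared: 0.686 for raw change, 0.611 for follow-up score.

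**4. Omitted balancing factors.** Take balance as complete, so that the true SE is the model SE × √(1 − R²).

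- Type I error = 2[1 − Φ(1.960/√(1 − R²))]
- Power, factors omitted = Φ((2.894 − 1.960)/√(1 − R²))
- Power, factors included = Φ(2.894/√(1 − R²) − 1.960)

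| R² | SE overstated by | Type I error | Power, omitted | Power, included | Gain |
|---|---|---|---|---|---|
| 0.05 | 2.6% | 0.044 | 0.831 | 0.844 | 0.013 |
| 0.10 | 5.4% | 0.039 | 0.838 | 0.862 | 0.024 |
| 0.20 | 11.8% | 0.028 | 0.852 | 0.899 | 0.047 |

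The proper comparison is across each row. Omitting balanced factors does not leave power at 0.825, because the estimate is already less variable than its model SE suggests.

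These figures are per cancer type, where tumour site is constant. For the pooled result, the gain from adding tumour site depends on how far mean fatigue differs between the two cancers, which the documents do not give.

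**The case against.** The strongest objection is that silence is not omission. This is a condensed article, and a covariate list is often left to a full protocol or SAP, neither of which is shown. Time and hospital are named as levels of a multilevel model, which need not be a full list of its terms. This stands in part. The description excludes no covariate, and the point lapses if the full plan already includes these terms. It is therefore put as an improvement to the model as described.

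Some stronger readings are tempting, but the documents do not support them:

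- **That baseline fatigue is left out.** Its use is unstated. The sample size is worded in terms of change, and a longitudinal model with time as a level may treat baseline as one of the repeated outcomes.
- **That the balancing factors are ignored.** Hospital is one of them and is in the model. Tumour site is fully accounted for in any analysis within one cancer type, so its absence matters only for the pooled result.
- **That the trial loses its planned power.** Unadjusted power is about 0.82 after drop-out, above 0.80, if SD 4 belongs to the quantity compared.
- **That the tests are invalid.** The mismatch with the allocation is conservative and does not inflate false positives.
- **That only an average over visits will be estimated.** The Data analysis section says the effect is tested at 18 weeks and at nine months. It leaves unwritten only the model term that yields those two effects.

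It is also fair to say that hospital already absorbs part of the variance due to the balancing factors, so an R² of 0.20 for the rest may be high.

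**Conclusion.** The point holds as a worthwhile improvement and does not reveal an error that threatens the trial. As described, the fatigue model accounts for time and hospital, and does not carry in baseline fatigue, tumour site for the pooled result, or the four other balancing factors. That analysis is valid and reaches the stated power, but gives intervals wider than they need be.

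The larger gain comes from the baseline score: power rises from about 0.82 to 0.86-0.98 (SD 4 as follow-up SD) or 0.88-0.95 (SD 4 as SD of change) for r between 0.3 and 0.7. The balancing factors add less, about 0.01-0.05 in power for R² between 0.05 and 0.20, and bring type I error back from 4.4%-2.8% towards 5%. The size of every gain rests on the assumed r and R². The direction does not, provided that the covariates predict fatigue.

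**What to change.** State one primary mixed model for the 18-week and 9-month fatigue scores, with:

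- arm, visit and arm-by-visit;
- baseline fatigue score as a covariate;
- hospital, as now;
- tumour site in the pooled analysis;
- age group, radiotherapy before chemotherapy, tissue expander (within breast) and gender (within colon);
- correlation between repeated visits of the same patient.

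Report the adjusted arm difference with its 95% CI at each visit from this model, and keep unadjusted mean differences as description. Fit the same model, without tumour site, within each cancer type.

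The cost is a few lines of analysis text. Every covariate is already collected, either for the allocation or at the baseline visit, and neither the sample size nor any trial procedure changes.
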